** Assessments **						
BPII score	x		x	x	x	x
KOOS	x		x	x	x	x
Adverse events		x	x	x	x	x

TT-distalisation–distalisation of tibial tubercle; BPII–Banff Patella Instability Instrument; KOOS–Knee Injury and Osteoarthritis Outcome Score.

The hypothesis of the trial is that the novel accelerated rehabilitation protocol will lead to faster recovery and improved functional outcome at 6, 12 and 24 weeks compared with the conservative rehabilitation protocol. The secondary hypothesis is that the complication rate will be similar for both protocols.

The primary outcome in this study will be knee ROM measured at 12 weeks postoperatively. A total difference regardless of the direction of the movement of 10° in full range of movement will be considered significant. The results will be measured with a long goniometer in a standardised manner. Secondary outcomes will be knee ROM measured at baseline, 6, 24 and 52 weeks postoperatively, the Knee Injury and Osteoarthritis Outcome Score (KOOS) and the Banff Patella Instability Instrument (BPII) score measured at baseline, 6, 12, 24 and 52 weeks, and isometric muscle strength measured at baseline, 12, 24 and 52 weeks postoperatively. Regained isometric muscle strength will be measured during follow-up visits and calculated to a ratio compared with a preoperative value. The number of reoperations and complications (failure of fixation and stress-fractures) will be also reported as secondary outcomes. The KOOS questionnaire is an instrument to assess patients’ opinions about their knees and any associated problems. KOOS consists of 5 subscales: Pain, other Symptoms, Function in daily living, Function in sport and recreation and knee related Quality of life. BPII is also a patient-reported outcome measurement instrument. BPII is, however, more specific for patellofemoral problems.

After enrolment, all the patients visit the study physiotherapist. The baseline scores from ROM, isometric muscle strength, KOOS and BPII are recorded during the visit. Randomisation to the allocation groups will be done after surgery.

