### Follow-up

Postoperative physiotherapy control visits will take place at 6, 12, 24 and 52 weeks after the procedure. The physiotherapy control visits will be managed by a senior physiotherapist who will be blinded to the allocation group. During the visits, knee ROM and isometric flexion/extension strength will be measured. The isometric extension and flexion strength will be measured with an SBS-KW-300SLIM scale. In addition, the PROMs (KOOS and BPI) will be collected during the research related control visits by the senior physiotherapist at previously defined time points (Table 2).

Postoperative physiotherapy sessions will be provided by physiotherapists who will not otherwise be involved in the study. Physiotherapy control visits and rehabilitation guidance sessions with the treating physiotherapist will take place at 1, 4, 6, 8, 12 and 24 weeks. The physiotherapy protocol will last for 24 weeks. Protocols 1 and 2 are presented in the supplementary material.

Healing of the osteotomy site will be evaluated with plain radiograph examination at 6 and 12 weeks after the procedure. The radiographs will be evaluated by an experienced radiologist and the operating surgeons. Physician visits will be at 6 and 12 weeks. Knee scores and isometric flexion/extension strength will be assessed preoperatively and at 12 and 52 weeks postoperatively.

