### Power analysis

We defined 10 degrees [10] in knee ROM in the primary end-point as a clinically relevant difference we would not like miss. We estimated a common standard population deviation of 20 degrees for knee ROM in both groups. Based on unadjusted t-test (TrialSize package in R), we need 63 patients per group to have a power of 80% with 5% type I error level. With this age group, the estimate of loss to follow-up rate will be set to 5% and will result in a total of 132 patients participating in the trial.

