### Statistical analysis

Study analysis will be done using mixed linear model allowing for repeated measures in longitudinal setting. All continuous variables will be analyses in this fashion. Each outcome variable will be the dependent variable and patient the random factor. Study group and time point will be included as fixed factor. Stratification variables are included as covariates in the analysis. If baseline value for the dependent variable (i.e. ROM) is available, it will be included also as a covariate. Treatment effects at each time point are the estimated marginal means for time point and study group interaction term. Satterthwaite method is used to estimate degrees in freedom in these analyses. No imputation is needed as liner mixed model is used and a full data set will be used in the analyses. Logistic regression is used to analyse binary outcome. Adjusted risk difference at each time point will be reported for complications and reoperations. All analyses will done with RStudio with suitable packages (i.e. *lmer* and *emmean*).

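### The reason given for needing no imputation covers missing follow-up values only; a patient without a baseline value would drop out of the mixed model for that outcome (minor)

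*Protocol article*

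**What the plan says.** All the analysis statements are in the protocol article under Statistical analysis. Continuous outcomes are analysed with a linear mixed model: patient is the random factor, study group and time point are fixed factors, and the stratification variables are covariates. On baseline it says "If baseline value for the dependent variable (i.e. ROM) is available, it will be included also as a covariate". On missing data it says "No imputation is needed as liner mixed model is used and a full data set will be used in the analyses". The software named is R with lmer. No rule is given for a patient whose baseline value is absent.

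The text below Table 1 sets the context. "The primary outcome in this study will be knee ROM measured at 12 weeks postoperatively". All patients see the study physiotherapist after enrolment, and "The baseline scores from ROM, isometric muscle strength, KOOS and BPII are recorded during the visit". Allocation comes later: "Randomisation to the allocation groups will be done after surgery". Under Follow-up, "Postoperative physiotherapy control visits will take place at 6, 12, 24 and 52 weeks after the procedure", so ROM gives up to four follow-up rows per patient.

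**The concern.** A likelihood-based mixed model uses whatever responses a patient has, so a missed visit costs only that visit. Covariates are treated differently: a row with a missing covariate cannot enter the likelihood and is removed. Baseline is constant within a patient, so one missing baseline value removes all of that patient's follow-up rows for that outcome.

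For such a patient the plan's two promises, no imputation and a full data set, cannot both be kept. Randomised patients with a measured 12-week ROM would leave the primary analysis. Each outcome has its own baseline, so the ROM, KOOS, BPII and strength analyses could also rest on different sets of patients. A missing baseline is possible because the baseline visit and randomisation are separate events, and the article does not make a complete baseline a condition of randomisation.

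**Working it through.** **1. The plan's own sample size.** Inputs from Power analysis: difference 10 degrees, SD 20 degrees, 80% power, 5% type I error (two-sided assumed), 63 per group, 5% loss to follow-up, 132 in total.

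- Normal approximation: n per arm = 2 × (1.960 + 0.842)² × (20/10)² = 62.8, so 63. The stated figure reproduces.
- The exact t-test gives 63.8, so 64.
- Total: 126 / 0.95 = 132.6, so 133 against the stated 132.

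These differences are immaterial and are not at issue here.

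**2. What the model does with missing values.** The model y ~ group × time + baseline + (1 | patient) was run on simulated data for 132 patients with 4 visits each, giving 132 × 4 = 528 rows.

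| Missing data | Rows usable | Patients usable |
|---|---|---|
| None | 528 | 132 |
| Week 52 response missing in 7 patients | 528 − 7 = 521 | 132 |
| Baseline missing in 7 patients | 528 − 7 × 4 = 500 | 132 − 7 = 125 |
| Same 7 patients, baseline filled with the overall mean | 528 | 132 |

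The third row was confirmed in lmer with default settings and the fourth in a Python mixed model. The second row is where the protocol's reason works, and the third is where it stops.

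**3. Can the conditional wording avoid this?** The clause about availability most naturally refers to the outcome variable: if that outcome has a baseline measurement, it is a covariate. ROM has one, so it enters, and patients without a value are dropped. If the clause is read patient by patient, a single fit cannot include the covariate for some patients and not others without imputation or a missing-indicator term. The plan calls the first unnecessary and does not mention the second.

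**4. Cost in power for 12-week ROM.** Expected patients with follow-up: 132 × 0.95 = 125.4, or 62.7 per arm. With a proportion m of baselines missing, 62.7 × (1 − m) per arm remain. The protocol gives no value for m; the range below is assumed. Power is for a two-sided 5% two-sample t-test.

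The first power column is unadjusted, with standardised difference 10/20 = 0.5. The other two allow for the gain from baseline adjustment by using 0.5 / √(1 − r²), where r is an assumed correlation between baseline and 12-week ROM, which the protocol does not give either.

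| m (assumed) | Per arm | Unadjusted | r = 0.2 | r = 0.3 |
|---|---|---|---|---|
| 0 | 62.7 | 79.3% | 80.9% | 82.9% |
| 2% | 61.4 | 78.5% | 80.1% | 82.2% |
| 5% | 59.6 | 77.2% | 78.9% | 81.0% |

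The normal approximation gives 79.9%, 79.1% and 77.9% for the unadjusted column. The loss is just under 1 point at 2% missing and about 2 points at 5%, whichever column is used. An extreme 10% missing would give 74.9% unadjusted, but nothing in the document suggests such a rate for ROM.

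**The case against.** The strongest reply is that the sentence is meant for missed follow-up visits, the only loss the article quantifies. For those it is the usual justification, valid when values are missing at random. A rule for an occasional missing covariate is detail that an analysis plan not shown here may contain. The trigger is also hypothetical: baseline is planned for every patient, in elective surgery at a single centre, and goniometer ROM is quick to measure.

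Most of this stands and sets the size of the point. It does not remove the point, because the article does not merely leave the matter open. It states that no imputation is needed and that a full data set will be used, and for the model in the same paragraph this does not follow.

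A reader might infer three stronger things that the document does not support:

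- **That dropping these patients biases the treatment effect or undermines the comparison by randomised group.** Baseline is recorded before allocation, so allocation cannot affect whether it is missing. The excluded patients are expected to be balanced between arms.
- **That the trial becomes underpowered.** The unadjusted figures rest on assumed missing rates and leave out the gain from the same adjustment that causes the deletion. With r = 0.3, power stays above 80% even at 5% missing.
- **That the covariate would be dropped for everyone if one patient lacked it.** The text does not say this.

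**Conclusion.** The point holds in a limited form and is minor. The stated reason is right for missing follow-up values and wrong for a missing baseline covariate. Each patient without a baseline value would lose up to four follow-up rows for that outcome, including 12-week ROM. The harm is some lost precision, incomplete inclusion of randomised patients with follow-up, and possibly different subsets across outcomes.

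The row loss is certain, given a missing baseline and default software behaviour. How often it will happen is unknown, and it is probably rare for ROM. The power figures are illustrations that depend on the assumed rates, on a two-sided test and, in the adjusted columns, on an assumed correlation.

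**What to change.** Replace the sentence on imputation with wording such as: Missing follow-up values are handled by the mixed model without imputation. A missing baseline covariate is replaced by the overall mean of that baseline variable, calculated over all randomised patients without regard to arm, so that every randomised patient with at least one follow-up value is analysed.

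Because the covariate precedes randomisation and the fill-in ignores arm, this does not bias the treatment contrast. A missing-indicator term, or modelling baseline as a response, would also serve. What matters is that one rule is fixed before allocation is revealed.

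One limit should be noted. The regained-strength outcome is itself a ratio to the preoperative value, so without that value the ratio is missing as a response, and filling in the covariate does not restore it.

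The cost is one sentence, one line of code and a slightly weaker covariate adjustment for the few patients concerned. Sample size, visits and data collection are unchanged.

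### Risk differences for rare complications and reoperations taken from a logistic model will usually carry intervals that are too narrow when an arm has no events

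*Protocol article*

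**What the plan says.** The Statistical analysis section of the Protocol article fixes the model for binary outcomes and the quantity to be reported: "Logistic regression is used to analyse binary outcome. Adjusted risk difference at each time point will be reported for complications and reoperations". The covariates are the two randomisation factors, age band and dislocation history: "Stratification variables are included as covariates in the analysis". On software it says only "All analyses will done with RStudio with suitable packages". It names no interval method for the risk difference and makes no provision for few or no events.

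The outcomes are set out in Materials and methods, below Table 1: "The number of reoperations and complications (failure of fixation and stress-fractures) will be also reported as secondary outcomes". The same text gives the hypothesis that these data serve: "The secondary hypothesis is that the complication rate will be similar for both protocols". It states no margin and no expected rate. The Interim analysis section adds that adverse and serious adverse events, among them superficial infection, persisting pain, deep infection, implant failure and non-union, will also count as complications in the final report.

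The only size given is for the range-of-motion endpoint: "we need 63 patients per group to have a power of 80% with 5% type I error level".

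**The concern.** Fixation failure, stress fracture and reoperation may each occur in only a few patients, and reporting at each time point thins the counts further. A logistic model fitted by maximum likelihood handles an empty arm badly. The fitted risk goes to 0, and so does that arm's share of the standard error, as if zero events in 63 patients proved a risk of exactly zero. The interval then reflects the uncertainty of the other arm only.

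With no margin and no test stated, readers will judge similarity of complication rates from the risk difference and its interval. If the accelerated arm truly does worse on a rare event, an upper limit that is too low understates the excess that the data still allow. The Introduction gives avoidance of implant failure, displacement and non-union as the reason for the usual restrictions, so these rare events are the ones of most interest.

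**Working it through.** **Inputs.** From the article: 63 analysed patients per arm (Power analysis); logistic regression, adjusted risk difference and two binary covariates (Statistical analysis). Assumed, because the article gives none: event rates of 1% to 10%.

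**The plan's own figure.** n per arm = 2 × (1.960 + 0.842)² × 20² / 10² = 62.8, so 63. Then 126 / 0.95 = 132.6, against 132 stated. The size reproduces, but it was set for range of motion and says nothing about complications.

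**Step 1: what an empty arm contributes.** Without covariates, the delta-method standard error of the risk difference from a logistic model is √[pA(1−pA)/63 + pC(1−pC)/63]. With pA = 0 the first term is 0. Adding two binary covariates does not change this. At 0 v 2 events (accelerated v conservative) the treatment coefficient runs to about −22.6 with a standard error of about 56,000, yet the fitted risk and its standard error are both 0.000. The exact 97.5% upper bound for 0/63 is 1 − 0.025^(1/63) = 5.7%. A patient bootstrap does no better, because resampling an arm without events always returns none.

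**Step 2: effect on the interval** (accelerated minus conservative, percentage points, unadjusted):

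| Events, accelerated v conservative | Wald | Miettinen-Nurminen |
|---|---|---|
| 0 v 0 | 0.0 to 0.0 | −5.8 to +5.8 |
| 0 v 1 | −4.7 to +1.5 | −8.5 to +4.3 |
| 0 v 2 | −7.5 to +1.1 | −10.9 to +2.7 |
| 0 v 3 | −10.0 to +0.5 | −13.1 to +1.2 |
| 3 v 0 | −0.5 to +10.0 | −1.2 to +13.1 |

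Worked line, 0 v 1: 1/63 = 1.59%; SE = √(0.0159 × 0.9841 / 63) = 1.57%; upper limit = −1.59 + 1.96 × 1.57 = +1.5. The adjusted logistic model gives +1.4.

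**Step 3: how often an arm is empty.** With the same rate p in both arms, P(at least one empty) = 1 − [1 − (1 − p)^63]². This is 78% at 1%, 48% at 2%, 27% at 3%, 8% at 5% and 0.3% at 10%.

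**Step 4: how often the upper limit falls below the true excess** (nominal 2.5%; exact enumeration of both binomial counts):

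| True rates, conservative v accelerated | Wald | Of which accelerated arm empty | Miettinen-Nurminen |
|---|---|---|---|
| 1% v 3% | 14.7% | 14.7 points | 0.4% |
| 2% v 4% | 7.8% | 7.6 points | 1.2% |
| 2% v 6% | 5.1% | 2.0 points | 1.1% |
| 3% v 6% | 4.6% | 2.0 points | 2.3% |
| 5% v 10% | 3.2% | 0.1 points | 2.2% |

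The third column follows from P(no events in the accelerated arm), for example 0.97^63 = 14.7%. With that arm empty, the Wald upper limit is at most about +1.5 points, so every true excess in the table is missed. At 1% v 3%, 0.99^63 × 0.97^63 = 7.8 points of the 14.7% are trials with no events in either arm.

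Two-sided Wald coverage is 84.7% at 1% v 3% and 90.9% at 2% v 4%. The percentile bootstrap misses 14.8%, 8.4% and 5.1% in the first three rows. A simulation of the adjusted logistic model (3,000 trials per row; age bands assumed 50:50 and dislocation history 70:30) gives 15.1%, 7.4%, 5.6%, 5.0% and 3.6% down the rows. Adjustment therefore does not remove the fault.

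**The case against.** The best reply is that the article does not say how the interval will be formed. Maximum likelihood with a delta-method or bootstrap interval is the usual reading of its text, but it is a reading. A statistical analysis plan that is not shown could name Firth's penalty or a score interval without contradicting the article. This stands as a limit on certainty. The published sentence still fixes a model whose usual intervals fail for rare events, and adds no safeguard.

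Three stronger readings are tempting and are not supported:

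- *That the fault arises however the interval is computed.* It does not. A profile-likelihood interval from the unadjusted likelihood gives −3.0 to +3.0% at 0 v 0. Its upper-limit miss is 6.9% at 1% v 3% and 5.7% at 2% v 4%. Both exceed 2.5%, but the interval does not collapse.
- *That the trial would rule out a harm that is present.* No margin or non-inferiority test is stated, so nothing is formally ruled out. At 0 v 0, which makes up more than half of the 14.7%, readers would see that no events occurred and would hardly trust a zero-width interval.
- *That the whole complication comparison is compromised.* The Interim analysis section also counts persisting pain and superficial infection as complications. A pooled count at about 10% or more would show almost no effect. From 2% v 6% upwards, most of the excess miss is ordinary Wald skewness, not an empty arm.

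Two further points stand. With equal true rates, Wald coverage is near or above nominal (94% to 99.6% at rates of 1% to 5%), so the failure appears when a true excess exists. And when the conservative arm is the empty one, its missing uncertainty belongs to the lower limit, although the upper limit still lies below the score limit (10.0 v 13.1 at 3 v 0).

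**Conclusion.** The concern holds for individual rare events. The planned model, with its usual delta-method or bootstrap interval, understates uncertainty when an arm has no events. The upper limit then misses a true excess in the accelerated arm about six times as often as it should at 1% v 3% (14.7 / 2.5 = 5.9) and about three times as often at 2% v 4% (7.8 / 2.5 = 3.1). The effect shrinks to 5.1% at 2% v 6% and 3.2% at 5% v 10%, and it is negligible for a broad composite at about 10% or more.

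These sizes rest on assumed event rates, on 63 analysed patients per arm, and on a delta-method or bootstrap interval being used. The change is worth making before the analysis because it is cheap and concerns a stated hypothesis. It does not touch the primary endpoint.

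**What to change.** In the Statistical analysis section, replace the sentence on complications and reoperations with one to this effect: the risk difference between arms will be reported with a 95% Miettinen-Nurminen score interval, stratified by age band and dislocation history with Mantel-Haenszel weights; any logistic regression will use Firth's penalty and be supporting only. A Newcombe interval is a reasonable alternative.

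Firth's penalty with a delta-method interval is not enough as the main analysis. At 0 v 1 its upper limit is +2.9 points, between the logistic +1.4 and the score +4.3. If Firth is kept as support, use profile-likelihood limits.

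The cost is one sentence and a standard R package. The risk difference and the adjustment for the stratification factors are kept. The downside is wider intervals, somewhat conservative when events are very few: a 0.4% miss at 1% v 3%, against 2.5% nominal.

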### Data management plan

Electronic portfolios provided by the Redcap application at Tampere university hospital’s server will be used to collect patient research data. Patients will be de-identified: each patient will be assigned a unique trial identification number (TIN), which is then matched with the patient’s personal identification number. The identification of each patient will only be possible after retrieving the matching key, which will be stored in a locked locker in the research nurse’s office at Pihlajalinna Koskisairaala Hospital. Access to patient research data will not be given to parties outside the trial. Throughout the trial, the research data will only be handled with a TIN.

Data will be saved electronically by patients and research personnel to Tampere University Hospital’s secure research server–Redcap (via tablets and laptops), which has been security cleared by the hospital district. The research data saved to the server will contain only pseudonymous TINs with a set of numbers acquired from the questionnaires; that is, each question is answered with a number. This will ensure the anonymity of each individual patient, and that the identity of the patient will remain secret, even if server data are revealed to third parties.

Each researcher participating in the trial will gain access to the data at the end of the trial for further analyses. All variables in the data set will be described, and suitable metadata standards will be used, when available.

The copyright of the trial research data will be owned and created by the participating research parties. The data will be shared among all participating researchers who will receive access to the data after the trial is completed. Due to confidentiality and legal agreements, public data sharing will be restricted because we only have permission to hold the data in the specific research server, not to transfer data. Under certain circumstances, for example, when a new member joins the collaboration, we will grant access to the data.

Members of study group have access to the password-protected study data for analysis. All research team members are bound by professional secrecy with respect to identifiable patient information. The results of the study will be published in a form that does not identify those individuals who participated in the study.

